### Evaluation plan

The evaluation framework will use a mixed-methods approach, where quantitative and qualitative data collection will occur using a concurrent dominant design. Mixed methods research involves collecting, analyzing, and interpreting quantitative and qualitative data in a single study that investigates the same underlying phenomenon [29]. Mixed methods research is useful for studying complex health issues such as motivations, attitudes, perceptions, beliefs, and values that underlie health behaviours within social, economic, organizational, and political contexts that cannot be captured by either quantitative or qualitative designs alone [30]. The primary outcome will be the change in the rate of transfers to ED from LTC facilities. Specifically, we will compare differences in the rate of transfers per 1000 resident days. This will be used to track the effectiveness of the intervention at the LTC sites (i.e., changes in the rate of transfer before and after the intervention). Data on all LTC-ED transfers are currently collected as part of administrative data by Alberta Health Service Analytics. Over the 30-month study period, our current rate of ED transfers would result in over 8000 LTC-ED transfers from patients within the 38 participating Calgary LTC facilities. After we account for the stepped-wedge design effects and plausible levels of over-dispersion, this will provide 80% power to detect a 15% reduction in the rate of LTC-ED transfers (primary outcome) [15, 31–33].

Secondary outcomes, using data obtained from administrative databases, will include the change in the rate of LTC admissions to hospital per 1000 resident days and the proportion of LTC residents cared for in their LTC facilities through community paramedicine post-pathway implementation. Consenting residents will also evaluate community paramedicine and ED care episodes by completing a modified version of the OPTICS (Older Persons Transition in Care Success; see Additional file 1) Success tool, within 2 days of a community paramedic visit or an emergency department visit that did not result in a hospital admission [31]. The OPTICS tool has been used and validated in previous studies [34, 37].

The appropriateness of the pathway triage decision will be assessed using a random

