### Study participants

Administrative data related to LTC resident visits by a community paramedic(s) and/or emergency department visits will be included for the 38 participating facilities. Consenting LTC residents and family members will complete the OPTICS tool with between five to 12 participants being recruited per facility. Residents will typically be long-stay residents. Fifteen to thirty eligible and consenting LTC residents and family members will participate in interviews. Thirty-six to seventy-two health care providers working within the participating LTC facilities, community paramedicine, and emergency departments will be asked to participate in focus groups.

Inclusion criteria for recruitment of residents or their family members include
LTC Resident has been seen by a community paramedic(s) OR has returned directly from the emergency department within the past 2 days (i.e., 72 hours) and they were not admitted to the hospital.The residents are not acutely confused.Must have a RAI CPS (Cognitive Performance Scale) score of 2 or less completed within the past 6 months.Do not have an enacted personal care directive (i.e., they are still able to make their own care decision)LTC Residents > 65 yearsIf the LTC resident does not meet these criteria but there is a family member who is regularly visiting the LTC resident, the family member can be approached while visiting the LTC facility for permission to be contacted.

Focus groups will be conducted with physicians, nurses, community paramedics and health care aides, who are direct care staff in LTC facilities. Inclusion criteria for LTC and ED health practitioners.
Physicians, staff (i.e., nurses and health care aides), or community paramedics associated with the LTC or ED must be familiar with or must have utilized the RAAPID pathway during the duration of the study.Nurses and health care aides must have used the INTERACT® and STOP and WATCH tools during the study to aid in their decision making.

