### Analysis plan

#### Quantitative analysis

The rate of transfers to ED from LTC facilities will be expressed as the number of ED transfers per 1000 resident days within each three-month cluster period. For our primary outcome, we will use a negative-binomial generalized linear mixed effects model. This model will have random intercepts for sites, an indicator variable for treatment mode in each cluster at each period and time, and fixed effects for time [15]. This model will account for Poisson over-dispersion, as well as correlations among observations within sites [31–33]. As a secondary analysis, we will use an individual-level analysis to determine whether the impact of the intervention depends on available patient-level factors (such as sex) and in a multilevel mixed-effects model with patient-level and site level effects. Generalized linear mixed-effects models will be used to assess a time by intervention effect on other outcomes using the link functions required to meet model assumptions [40].

Descriptive statistics will be used to determine the proportion of LTC residents cared for in their LTC facilities by the community paramedicine program, using the new LTC-ED care and referral pathway. This will be expressed as the number of Mobile Integrated Health (MIH) community paramedic LTC visits per total RAAPID calls from LTC. Descriptive statistics will also be used to present data on the appropriateness and safety of the pathway triage decision. The median and interquartile range will be calculated for the modified OPTICS tool scores for each of the three groups: pre-intervention ED transfer, post-intervention ED transfers, and post-intervention community paramedicine visits. Time series analysis will be used to compare the different groups.

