### Ethical considerations

This study protocol has received approval from the University of Alberta Research Ethics Board (Pro 00090932) and the University of Calgary Conjoint Research Ethics Board (REB190106). The study received funding from Alberta Innovates Health Solutions and AHS. Informed consent will be sought from LTC residents or their family members to participate in the OPTICS tool survey, chart abstractions, and/or interviews. Health care practitioners involved with LTC, EMS or the ED will also consent to participate in focus group sessions.

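### The OPTICS respondent is the resident in one section and the resident or a family member in two others, and the stated three-group comparison combines the two without regard to who answered

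*Protocol article*

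**What the plan says.** Three sections of the protocol article say who completes the modified OPTICS tool.

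- **Evaluation plan:** "Consenting residents will also evaluate community paramedicine and ED care episodes by completing a modified version of the OPTICS" tool. Only residents are named.
- **Study participants:** "Consenting LTC residents and family members will complete the OPTICS tool with between five to 12 participants being recruited per facility". Family members are now included.
- **Ethical considerations:** "Informed consent will be sought from LTC residents or their family members to participate in the OPTICS tool survey". Family members are included again.

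The criteria in Study participants require a resident who is not acutely confused, is over 65 and has no enacted directive. On cognition they add: "Must have a RAI CPS (Cognitive Performance Scale) score of 2 or less completed within the past 6 months". Where the resident does not meet the criteria, a regularly visiting relative may be approached instead.

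Quantitative analysis sets out the summary and the comparison. A median and interquartile range are given "for each of the three groups: pre-intervention ED transfer, post-intervention ED transfers, and post-intervention community paramedicine visits". Then: "Time series analysis will be used to compare the different groups". Respondent type is not mentioned in either sentence.

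**The concern.** The sections disagree on whether OPTICS is a resident-only measure or one with two kinds of respondent. Under the second reading the kind of respondent is not assigned at random, because the family route opens when the resident fails a criterion, and several of the criteria concern cognition and capacity.

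The analysis groups are defined by period and type of care alone. A group's median therefore depends on its mix of resident and family forms as well as on how the care was rated. If that mix differs between the ED groups and the paramedicine group, or between the ED groups before and after implementation, a difference in scores cannot be attributed to the care alone. If respondent type is not recorded at collection, it may be impossible to separate the two later.

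**Working it through.** **Comparing the sections.** The Evaluation plan names residents. Study participants and Ethical considerations name residents and family members. The last two agree with each other, and Study participants is the section devoted to recruitment, so the mixed rule is the more likely intention. The Evaluation plan sentence is the one out of line.

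**What the analysis does with the answers.** There are three groups: ED before the intervention, ED after it, and paramedicine after it. Each gets a median and IQR, and the groups are then compared. Nothing in this divides the forms by respondent, so resident and family forms enter together.

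**Whether the family share could differ between groups.** The Intervention section describes a call-centre discussion that weighs ED transfer against a paramedicine visit, so clinical state helps to decide which group an episode joins. The same process may change which residents reach the ED after implementation. Acute confusion is part of clinical state and also triggers the family route. A difference in shares is therefore plausible, but no figure in the documents shows one.

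**Scale.** The plan states no OPTICS effect size, SD or power, so there is no figure of its own to reproduce. The inputs are:

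- From the documents: 38 facilities and 5 to 12 participants per facility, read as residents and family together.
- Assumed: an even split over three groups, a family-minus-resident score gap of 0.3 to 0.5 SD, and family shares 20 to 40 points apart.

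Implied total: 38 × 5 = 190 to 38 × 12 = 456. Per group: 190 / 3 ≈ 63 to 456 / 3 = 152.

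SE of a two-group difference in means, in SD units and before clustering, is √(2/n):

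- n = 63.3: √(2/63.3) = 0.178
- n = 152: √(2/152) = 0.115

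Shift in the contrast = (difference in family share) × (score gap):

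| Difference in share | Gap (SD) | Shift (SD) | Shift / SE, total 190 | Shift / SE, total 456 |
|---|---|---|---|---|
| 0 | any | 0 | 0 | 0 |
| 0.20 | 0.3 | 0.06 | 0.3 | 0.5 |
| 0.30 | 0.5 | 0.15 | 0.8 | 1.3 |
| 0.40 | 0.5 | 0.20 | 1.1 | 1.7 |

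The formula applies to means, whereas the plan reports medians, so the table indicates scale only. Clustering by facility would normally enlarge the SE and lower the ratios. A larger sample does not reduce the shift.

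**The case against.** Much of the case on the other side stands.

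- **The respondent question is largely settled.** Two sections include family members, and the Evaluation plan sentence does not say that only residents respond. A reader might infer that residents who fail the criteria go unrepresented. That would require ignoring both of the other sections. What remains on this part is a correction of wording.
- **Pooling is not stated.** It follows from how the three groups are defined. The article does not rule out strata or covariates, and the unseen analysis plan or the tool in Additional file 1 might already deal with respondent type. This limits the point but does not remove it: the comparison that is written down has no place for respondent type, and the sections still conflict.
- **Proxy report is an inference.** A reader might take the family forms to be answers given for the resident. The documents do not say whether relatives answer for the resident or rate their own experience. The plan lists resident and family experience among its evaluation targets, so the relative's own view may be wanted.
- **The link to the episode is partial.** The CPS score may be up to 6 months old, nothing ties an enacted directive to the episode, and the age criterion can open the family route whatever the resident's cognition. Only acute confusion is clearly tied to the episode. The Background says that ED transfer can lead to cognitive decline but gives no timing, so it does not show that shares differ within days of the visit.
- **OPTICS is secondary** and carries no power claim.

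**Conclusion.** The point holds in a limited form. The sections conflict on who completes OPTICS, and the stated comparison combines resident and family answers although the family route is opened by resident characteristics. If family shares differ between groups, part of an OPTICS contrast could reflect who answered.

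A reader might conclude that the ED-versus-paramedicine contrast is biased. The documents do not support that, because they give neither the shares nor the gap between respondents. Over the assumed values the shift in means runs from zero, with equal shares, to 0.20 SD at the upper end of both assumptions. Only the implied total of 190 to 456 comes from the plan's own figures.

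This concerns one secondary outcome. The primary outcome, the ED transfer rate from administrative data, is unaffected. The change is worth making because it is cheap now and may not be recoverable after collection.

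**What to change.** 1. In the Evaluation plan, say that residents or family members complete OPTICS, in line with Study participants and Ethical considerations. State whether a family member answers for the resident or rates their own experience.
2. Record respondent type on every form.
3. In Quantitative analysis, report medians and IQRs by respondent type within each of the three groups. Compare the groups with respondent type as a stratum or covariate, and show a resident-only comparison alongside.

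The cost is one recorded field and a slightly longer analysis, with smaller strata and slightly wider intervals.

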**Fig. 3 Fig3:**
[figure not shown]
Logic model of the major components of the study

### Study participants

Administrative data related to LTC resident visits by a community paramedic(s) and/or emergency department visits will be included for the 38 participating facilities. Consenting LTC residents and family members will complete the OPTICS tool with between five to 12 participants being recruited per facility. Residents will typically be long-stay residents. Fifteen to thirty eligible and consenting LTC residents and family members will participate in interviews. Thirty-six to seventy-two health care providers working within the participating LTC facilities, community paramedicine, and emergency departments will be asked to participate in focus groups.

Inclusion criteria for recruitment of residents or their family members include
LTC Resident has been seen by a community paramedic(s) OR has returned directly from the emergency department within the past 2 days (i.e., 72 hours) and they were not admitted to the hospital.The residents are not acutely confused.Must have a RAI CPS (Cognitive Performance Scale) score of 2 or less completed within the past 6 months.Do not have an enacted personal care directive (i.e., they are still able to make their own care decision)LTC Residents > 65 yearsIf the LTC resident does not meet these criteria but there is a family member who is regularly visiting the LTC resident, the family member can be approached while visiting the LTC facility for permission to be contacted.

Focus groups will be conducted with physicians, nurses, community paramedics and health care aides, who are direct care staff in LTC facilities. Inclusion criteria for LTC and ED health practitioners.
Physicians, staff (i.e., nurses and health care aides), or community paramedics associated with the LTC or ED must be familiar with or must have utilized the RAAPID pathway during the duration of the study.Nurses and health care aides must have used the INTERACT® and STOP and WATCH tools during the study to aid in their decision making.

### Analysis plan

#### Quantitative analysis

The rate of transfers to ED from LTC facilities will be expressed as the number of ED transfers per 1000 resident days within each three-month cluster period. For our primary outcome, we will use a negative-binomial generalized linear mixed effects model. This model will have random intercepts for sites, an indicator variable for treatment mode in each cluster at each period and time, and fixed effects for time [15]. This model will account for Poisson over-dispersion, as well as correlations among observations within sites [31–33]. As a secondary analysis, we will use an individual-level analysis to determine whether the impact of the intervention depends on available patient-level factors (such as sex) and in a multilevel mixed-effects model with patient-level and site level effects. Generalized linear mixed-effects models will be used to assess a time by intervention effect on other outcomes using the link functions required to meet model assumptions [40].

Descriptive statistics will be used to determine the proportion of LTC residents cared for in their LTC facilities by the community paramedicine program, using the new LTC-ED care and referral pathway. This will be expressed as the number of Mobile Integrated Health (MIH) community paramedic LTC visits per total RAAPID calls from LTC. Descriptive statistics will also be used to present data on the appropriateness and safety of the pathway triage decision. The median and interquartile range will be calculated for the modified OPTICS tool scores for each of the three groups: pre-intervention ED transfer, post-intervention ED transfers, and post-intervention community paramedicine visits. Time series analysis will be used to compare the different groups.

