**Fig. 1 Fig1:**
[figure not shown]
Implementation of a stepped wedge design

By the end of the study, all 38 participating LTC facilities will have received the intervention. However, the order in which facilities receive the intervention will be determined at random [14]. A stepped-wedge design is an ideal design to evaluate an intervention on a population level, where there are implementation resource constraints. This design is also useful where there are ethical or community concerns that all participating sites should eventually get the intervention. As a crossover design, it also controls for confounding and site-level differences because each site is observed before and after the intervention. Therefore, changes within the wider health system over time can be observed, given data is available from multiple pre-intervention and intervention sites at various points in time [15].

The intervention will be implemented at four to five LTC facilities each quarter (every 3 months), with all facilities having implemented the intervention in 30 months. The pre-implementation phase will take place over 1 month. During the pre-implementation phase the researchers contact the participating sites, meet with site leaders and staff, conduct a barriers to implementation assessment, provide the overarching rationale for the implementation program and outline the plan for implementation (i.e., setting an implementation workshop and determining what additional resources are required). Baseline data with the OPTIC tool and chart abstractions will be done prior to the intervention, with implementation occurring over the subsequent 2 months. The intervention will then become an expected standard care practice at the facility, and thus this will be considered the post-implementation phase.

The order of implementation will be randomized using random number generation to reduce bias, where the unit of randomization is the LTC facility. LTC facilities with the same owner-operator will be randomized to the same implementation period, given that these facilities often share staff. Until the pathway is implemented at a LTC facility, facilities will act as controls for the purposes of analysis.

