#### Cost analysis

Comparative cost-analysis will be undertaken from the perspective of the publicly funded health care system. Health care costs will include hospitalizations, ED visits, ambulatory care, urgent care center, physician, and paramedic costs. Patient-level cost data will be provided by Data Integration, Measurement & Reporting (DIMR) at AHS. DIMR provides administrative data on costs as well as patient characteristics and diagnoses (ICD-10 codes). Physician costs are based on the fee for service physician billing to Alberta Health or, for those involved in alternative re-imbursement plans, shadow billing is used. Hospital costs are based on facility-specific costs per day and include direct costs and indirect costs such as diagnostic imaging, laboratory, housekeeping, administration etc. Monthly total costs will be calculated per patient by summing across all available cost data. A generalized linear model with random effects controlling for time and patient characteristics such as age and sex will be used to estimate the difference in costs with and without the program. Program costs, which are fully captured by our operational budget, will include wages, training, transportation, implementation resources, and IT costs. The difference in health care costs will be calculated and compared to program costs. These analyses will be used to evaluate the program’s return on investment. Costs will be reported at seven and 30 days.

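### Read literally, the mixed models for other outcomes test whether the effect changes over time, not whether the pathway works, and no other analysis is stated for hospital admissions

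*Protocol article*

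**What the plan says.** The Quantitative analysis section sets out a negative-binomial mixed model for the primary outcome, the ED transfer rate. It has random intercepts for sites, plus "an indicator variable for treatment mode in each cluster at each period and time, and fixed effects for time". Treatment and time enter as separate terms, and no interaction is mentioned.

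Later in the same paragraph the target for everything else is worded differently: "Generalized linear mixed-effects models will be used to assess a time by intervention effect on other outcomes", with link functions chosen to suit each outcome.

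The Evaluation plan names as a secondary outcome "the change in the rate of LTC admissions to hospital per 1000 resident days". The sentence about other outcomes does not list the outcomes it covers.

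**The concern.** In a mixed model, a time-by-intervention effect is the usual name for an interaction term. It is a natural effect measure in a parallel-group study with a shared baseline, where the groups are expected to diverge after the start. In a stepped wedge each facility moves from control to intervention, so the treatment indicator already changes within facility. Adjusted for period, its coefficient is the intervention effect. Adding time by intervention asks a further question: does that effect grow, shrink or stay the same?

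An analyst who follows the sentence and reports the interaction could find nothing for hospital admissions although the pathway reduces them steadily. Conversely, a change in the effect over time could be reported as if it were benefit. The admissions result would also not be on the same footing as the primary result, although both are rates per 1000 resident-days.

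**Working it through.** **1. Which outcomes depend on this sentence.** Each quantitative outcome, set against its stated method:

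- ED transfer rate (primary): negative-binomial mixed model with a treatment indicator and time effects.
- Share cared for through community paramedicine: descriptive ("Descriptive statistics will be used to determine the proportion of LTC residents cared for in their LTC facilities by the community paramedicine program").
- Appropriateness and safety: descriptive ("Descriptive statistics will also be used to present data on the appropriateness and safety of the pathway triage decision").
- OPTICS scores: median and interquartile range by group, then "Time series analysis will be used to compare the different groups".
- Costs: a random-effects model that "will be used to estimate the difference in costs with and without the program", controlling for time (Cost analysis).
- Hospital admission rate: no method of its own.

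The individual-level analysis in the same paragraph asks whether the impact depends on patient-level factors; it does not supply an overall effect for admissions. That leaves the sentence on other outcomes.

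**2. The algebra.** For facility i in period t, with treatment indicator x:

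log(rate) = site(i) + period(t) + x(i,t) × [θ + δ × time]

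The log rate ratio at a given time is θ + δ × time. If it equals ln(0.85) = -0.1625 at every time, then θ = -0.1625 and δ = 0. The same holds if time is counted from each facility's own start.

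**3. The plan's own power figure.** The article gives 80% power for a 15% reduction with over 8000 transfers, for the primary outcome only. It cannot be reproduced exactly, because alpha, dispersion, intracluster correlation and cluster sizes are not stated. With two-sided 0.05, an equal split and no design effect, the events needed are 4 × (1.960 + 0.842)² / 0.1625² ≈ 1189, so 8000 events leave room for a design effect of about 8000/1189 = 6.7. The figure is attainable and is not in dispute.

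**4. Both terms in an assumed wedge.** From the article: 38 facilities ("By the end of the study, all 38 participating LTC facilities will have received the intervention"), four to five per quarter, 30 months, about 8000 events, rate ratio 0.85. Assumed: 10 quarterly periods, 9 steps, equal facility sizes, no underlying trend, site effects taken as fixed, and a range of dispersions d. Mean count per facility-quarter without the intervention is 8000 / (38 × 10 × 0.925) = 22.8, where 0.925 is the midpoint of 1 and 0.85. The negative-binomial weight is μ/(1 + dμ). Power is Φ(|estimate|/SE − 1.96), plus a negligible opposite tail.

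| d | SE, intervention (no interaction) | Power, intervention | Interaction with calendar time | SE, interaction | Rejection, interaction |
|---|---|---|---|---|---|
| 0 | 0.0392 | 99% | 0 | 0.0158 | 5% |
| 0.02 | 0.0467 | 94% | 0 | 0.0188 | 5% |
| 0.05 | 0.0561 | 83% | 0 | 0.0226 | 5% |
| 0.10 | 0.0690 | 65% | 0 | 0.0278 | 5% |
| 0.20 | 0.0894 | 44% | 0 | 0.0359 | 5% |

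For example, at d = 0.05: 0.1625/0.0561 = 2.90 and Φ(2.90 − 1.96) ≈ 0.83. The stated 80% corresponds to d slightly above 0.05. An interaction with time since each facility's start also gives 0 and 5% throughout.

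The power column uses the primary outcome's event count. The article gives none for admissions, so those powers do not carry over. The last column does carry over, because a true value of zero is rejected at alpha whatever the event count or dispersion.

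**The case against.** The strongest reply is that the phrase is loose. The article gives no equation and no named coefficient, it defines the admissions outcome as a change in rate, its cost model estimates a with-versus-without difference, and no objective concerns drift in the effect. The authors may have meant the intervention effect in a model with time, or a difference-in-differences contrast, which in a stepped wedge is the treatment indicator. That is possible. But the same paragraph has just described such a model with treatment and time as separate terms, and nothing says that the later phrase means the same. Under the loose reading the sentence still names the wrong quantity.

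It is also fair that admissions are assigned to this sentence by elimination, that a model with the interaction would normally contain the intervention term too, and that a condensed article may leave model detail elsewhere. The first two limit how firmly harm can be predicted. The third does not remove the point, because the article states which effect will be assessed rather than leaving it open.

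Three stronger readings are not supported:

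- A reader might infer that adding the interaction destroys power for the intervention term. That depends on where time is counted from, which the article does not state. With d = 0.05 and time counted from the sixth quarter, near mid-study, the SE goes only from 0.0561 to 0.0566 and power stays at about 82%. A large loss arises only if the intervention term is read at or before the first period, when in the assumed layout no facility is treated.
- A reader might infer that the interaction cannot be estimated. That is true only of a fully categorical interaction, in periods when all facilities are in one state. A linear one can be estimated.
- A reader might infer that the trial's main conclusion is at risk. The primary model does not use this term.

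**Conclusion.** Wrong as written, for secondary outcomes only. Taken literally, the sole stated analysis for the hospital admission rate targets a quantity that is zero under a constant proportional reduction and is then declared significant only at alpha (5% if two-sided 0.05 is used, which the article does not state).

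This rests on three things: reading the phrase as an interaction; placing admissions under other outcomes by elimination; and a log link. With another link, such as identity, a constant rate ratio combined with changing baseline rates would not give exactly zero, but the interaction would still not be the intervention effect. The result does not depend on the dispersion, the number of events or the coding of time. The primary analysis and its stated power are unaffected.

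**What to change.** Replace the sentence with wording such as: *For the hospital admission rate and any other repeated outcome analysed by generalized linear mixed models, the effect is the coefficient of the intervention indicator in the same model form as the primary outcome: fixed effects for period, random intercepts for sites and, for rates, resident-days as exposure. A time-by-intervention term may be added as an exploratory check of whether the effect is constant; if so, the time scale and its coding will be stated.*

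Listing the outcomes that the sentence covers would remove the need to infer it. The cost is one sentence, with no new data and no change to the design or sample size. If the loose meaning was intended, the edit only records it. It should be settled before outcome data are analysed.
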